### 1.3. Trial Design

This is a protocol for a single-blind, two-armed randomized controlled trial evaluating changes in primary and secondary outcomes post-intervention and follow-up. The two arms will be: (a) the intervention, which comprises eight internet-based modules of CBT delivered over 10-weeks using the program Reframe-IT and four 45-min face-to-face psychotherapeutic CBT sessions, and (b) control group (Treatment-As-Usual) (see Table 1).

## 2. Methods: Participants, Interventions, and Outcomes

Trial registry: ClinicalTrials.gov: NCT05229302. Registered 8 February 2022.

### 2.1. Study Setting

Participants will be adolescents attending schools with secondary education (grades 9–11), mixed sex, located in three different cities in the South of Chile, with at least two classes per year. We expect to recruit at least ten schools per arm. Each arm should include 140 eligible students.

#### Eligibility Criteria

Inclusion criteria for the present study are:Secondary students attending grades 9–11.High scores in suicidal ideation, last month (score ≥ 3 in the Columbia Suicide Severity Rating Scale (C-SSRS) [58].Fluent in the Spanish language.

The exclusion criteria are:Suicide attempt(s), last month.Severe depressive symptoms assessed by the PHQ-9 (>19 points).High severity of psychotic symptoms assessed by the Community Assessment of Psychic Experiences-Positive scale (CAPE, P15) [59]; (cut-off = 1.47) [60].

### 2.2. Recruitment and Informed Consent

The schools will learn about the study through invitations made to their institutional email and social networks. Eligible schools will be invited to participate through letters sent to the authorities, who will sign an agreement letter to participate in the study. This research project has the approval of the Scientific Ethics Committee of the Universidad de Talca (12 May 2021). At the beginning of the academic year, we will send a letter to the emails with information about the study, inclusion and exclusion criteria, screening instruments, the selection process, and the written consent to all parents or main caregivers of students. The informed and written consent will be signed digitally through Qualtrics. Qualtrics is a platform that allows information to be collected online with high security standards and that also can facilitate the digital signature through a cell phone or tablet (using the finger) or through a computer (with a mouse). Additionally, all students attending grades 9–11 of selected schools will be invited to participate through informative talks about the study. All students will be asked for written assent. All consented/assented students will be surveyed with the following screening questionnaires during the second month of the academic year: the Columbia Suicide Severity Rating Scale (C-SSRS) [58]; PHQ-9 [61]; and the Community Assessment of Psychic Experiences-Positive (CAPE-P15) [59]. The Qualtrics platform will also be used to collect data of screening instruments: suicidal ideation (SI) and suicide attempts (C-SSRS), depressive symptoms (PHQ-9), and psychotic symptoms (CAPE-P15). These data will be used for the study eligibility analysis. All who report any level of SI during the previous month (score ≥ 3 in the C-SSR) will be invited to participate in the following step of the study. Informed consent will cover general screening, baseline measurements, and follow-up during and after the intervention.

### 2.3. Additional Consent Provisions for Collection and Use of Participant Data and Biological Specimens

Not applicable. No biological samples will be collected.

## 3. Interventions

### 3.1. Explanation for the Choice of Comparators

All participants in the intervention group will be sent to primary care centers, where a protocol for managing suicidal ideation defined by the Chilean Ministry of Health will be applied [62]. The whole procedure will be described as Treatment-As-Usual (TAU). TAU consists of identification and assisted referral to a primary care clinic, where trained psychologists will assess the symptomatology and propose a course of actions, from initiation of psychotherapy to referral to a general practitioner to initiate medication if needed. Psychotherapy in primary care clinics consists of a range of 4–8 sessions twice a month. Most of the content of the psychotherapy is based on the Cognitive-Behavioral Model. When needed, general practitioners may suggest using medications, which generally are SSRI antidepressants (e.g., Fluoxetine, Sertraline). A medical check-up is conducted every month or every two months.

The control group will receive the Treatment-As-Usual (TAU). In order to reduce the risk of performance bias, all adolescents who need to have care in a public health center will receive the same treatment. The public health centers have similar structures and resources, they have standardized protocols for managing mental disorders and suicide risk and the professionals have similar backgrounds and skills. To test potential biases, we will register and quantify all different interventions delivered by health centers.

### 3.2. Intervention Description

#### 3.2.1. Experimental Intervention

##### Internet-Based Component (Reframe-IT)

It has been described elsewhere [46,48]; it comprises eight modules of CBT delivered over a 10-week intervention period. The program will be administered at schools by trained school psychologists (one psychologist per school). The authors will deliver the training of the program. Each participant will have access to their personalized web page accessed via secure login. Each module will be completed in the psychologist’s presence and participants will also be able to access it at home 24 h a day. For safety reasons, the program does not have social networking functions. Standard CBT approaches are delivered in the intervention, focusing on SI and behaviors. The modules and their respective topics are: -Module 1: engagement and problem identification;-Module 2: emotional recognition and distress tolerance;-Module 3: identification of automatic negative thinking;-Module 4: behavioral activation help seeking;-Module 5: behavioral activation activity scheduling (including relaxation techniques);-Module 6: problem solving;-Module 7: cognitive restructuring;-Module 8: wrap-up session.

These contents are delivered via a series of video diaries by young people as main characters with an adult ‘host’ character highlighting the CBT contents presented in the context of the video diaries. There are two activities per module. Overall, each module lasts about 25 min. The site has a message board through which the participant could communicate with research therapists (clinical psychologists), who also check completed activities and respond with personalized but standardized messages. Finally, a series of fact sheets cover various related topics including managing SI, plus downloadable relaxation MP3s.

##### Face-to-Face Intervention

We developed four face-to-face CBT sessions following a similar structure of the Reframe-IT sessions (brief videos, activities, and mood checking). Each session lasts about 45 min. The aims of the sessions are described as follows:

Session 1: To improve the participant’s literacy on emotions, reinforcing the following contents: the usefulness of emotions, the emotions and our body, the intensity of emotions, and the critical point. Moreover, the session trains on a breathing technique to favor relaxation.

Session 2: to reinforce the capability to identify negative thoughts and to understand the associations between thoughts, emotions, and behaviors. 

Session 3: to reinforce the usage of a problem-solving method presented in Reframe-IT (SMART Plan), which helps to assess the potential solutions and their consequences to improve outcomes. 

Session 4: To improve the capability of cognitive restructuring. Participants are encouraged to recognize negative automatic thoughts and related emotions to improve the identification and management of potential solutions. 

### 3.3. Criteria for Discontinuing or Modifying Allocated Interventions

Participants in the intervention group can leave the study at any time if they wish without any consequences; this means that their information and collected data will not be analyzed. On the other hand, the control group will keep its condition during the whole trial, but they also can leave the study at any time if they wish without any consequences.

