### 3.8. Sample Size

This sample size considers a loss at follow-up of 20% of the students. Considering a 20% of school rejection at the recruitment stage, we expect to recruit 12 schools. Studies of similar school-based interventions report effect sizes of at least 0.4 standard deviation using symptoms questionnaires as proposed here [71]. We used the results previously observed by Hetrick et al. [49] and the clustersampsi command in Stata Software to estimate the number of clusters in two arms, using the following command: clustersampsi, samplesize mu1(X1) mu2(X2) sd1(Y1) sd2(Y27) m(Z) rho(R). Where X1 = mean in arm 1; X2 = mean in arm 2; Y1 = standard deviation (SD) in arm 1; Y2 = SD in arm 2; Z = number of children per school on average (harmonic mean) (*n* = 14); and R = intracluster correlation. The two arms will be balanced for school size. 

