## 7. Statistical Methods

### 7.1. Statistical Methods for Primary and Secondary Outcomes

We will use descriptive statistics to assess balance across arms at baseline. The primary between-group analysis will be carried out on an intention-to-treat basis for 3-month SIQ scores. We will use linear mixed effects model analysis to compare the intervention and control groups regarding the change in outcome measures from baseline to post-intervention and the follow-up time point. The school is included as a random factor for each outcome measure to account for possible school effect. We will use Fisher’s exact test to compare the frequency of suicide attempt cases between groups. We also will conduct a Complier Average Causal Effect (CACE) analysis to assess the impact of the number of sessions on the primary outcome. All analyses will be performed using STATA 15.01. 

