### 7.4. Methods in Analysis to Handle Protocol Non-Adherence and Any Statistical Methods to Handle Missing Data

The primary outcome will be assessed using an intention-to-treat analysis. Missing data will be reduced to a minimum by using the appropriate measures; encouraging students to fill out the whole questionnaire, a research assistant will revise the questionnaire when students end the evaluation and ask to complete the instruments if some questions are unanswered. Multiple imputations will be used to handle missing data in the primary and secondary analyses.

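### Discarding the data of intervention-group students who leave contradicts the planned intention-to-treat analysis

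*Protocol article*

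**What the plan says.** Section 3.3 of the protocol article deals with leaving. For one arm it states: "Participants in the intervention group can leave the study at any time if they wish without any consequences". The same sentence continues: "this means that their information and collected data will not be analyzed". For the other arm it says that "the control group will keep its condition during the whole trial, but they also can leave the study at any time", with the same assurance that leaving carries no penalty. It does not mention what happens to control students' data.

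The statistical sections set a different rule. Section 7.1: "The primary between-group analysis will be carried out on an intention-to-treat basis for 3-month SIQ scores". Section 7.4: "The primary outcome will be assessed using an intention-to-treat analysis", and "Multiple imputations will be used to handle missing data in the primary and secondary analyses". Section 7.1 also plans a "Complier Average Causal Effect (CACE) analysis to assess the impact of the number of sessions on the primary outcome" and a Fisher's exact test on suicide attempts.

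The only attrition figure is in Section 3.8: "This sample size considers a loss at follow-up of 20% of the students".

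**The concern.** Intention-to-treat means that every randomised student counts in the allocated arm. Section 3.3 takes some of them out after randomisation, because of something they did after randomisation. Leaving a programme for suicidal ideation may well be related to how the student is doing. Section 5.2 also says that participants know their group, so the reasons for leaving may differ by arm. The main result could then be labelled intention-to-treat when it is not.

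Two other planned analyses are exposed as well. The CACE analysis needs intervention students with few sessions, and leavers are likely to include many of them. In the comparison of suicide attempts, an attempt already reported by an intervention student who later leaves would drop out of the count. The text states no matching rule for controls. For an uncommon, safety-relevant event, a few such cases could matter.

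**Working it through.** **The rules side by side.** The plan gives no figure of its own to reproduce on this point; the conflict is between texts. What happens to an intervention student who leaves depends on when:

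- *Leaves before the 3-month SIQ.* The 3-month score is missing. Under Section 7.4 it would be imputed, using the baseline score and any post-intervention score. Under Section 3.3 those scores are not analysed, so the student disappears from the analysis set.
- *Leaves after the 3-month SIQ but before the 6- or 12-month assessment.* The primary outcome has been observed. Under Sections 7.1 and 7.4 it counts. Under Section 3.3, read literally, it is set aside.

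In both cases Section 3.3 and Sections 7.1/7.4 give different analysis sets, and no section says which prevails. Nothing limits the exclusion to students who ask for their data to be withdrawn.

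**Size, if one arm only is affected.** Let p be the share of the arm removed, μ_L the mean of leavers and μ_S the mean of stayers.

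- Mean of the whole arm: (1 − p)·μ_S + p·μ_L
- Mean after exclusion: μ_S
- Bias = p·(μ_L − μ_S) in absolute size, assuming that all control students are fully retained

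Inputs:

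- p = 0.20 is borrowed from the Section 3.8 allowance for loss to follow-up. It is not a stated withdrawal rate, so it serves as an upper illustration. p = 0.10 is a further assumption.
- A leaver–stayer gap of 0.25, 0.5 or 1.0 SD is an assumption; the documents give none.
- The yardstick is the effect of at least 0.4 SD cited in Section 3.8.

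| p | gap (SD) | bias (SD) | share of 0.4 SD |
|---|---|---|---|
| 0.20 | 0.25 | 0.20 × 0.25 = 0.05 | 12.5% |
| 0.20 | 0.5 | 0.20 × 0.5 = 0.10 | 25% |
| 0.20 | 1.0 | 0.20 × 1.0 = 0.20 | 50% |
| 0.10 | 0.5 | 0.10 × 0.5 = 0.05 | 12.5% |
| 0.10 | 1.0 | 0.10 × 1.0 = 0.10 | 25% |

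In students, 20% of the 140 per arm in Section 2.1 is 0.20 × 140 = 28 removed, leaving 112.

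**Size, if both arms are affected.** The bias becomes the difference of two such terms: p_I·gap_I − p_C·gap_C, where I is intervention and C is control. With equal shares and equal gaps the two terms cancel. With, say, 20% against 10% leaving and a gap of 0.5 SD in both arms (assumptions), it is 0.10 − 0.05 = 0.05 SD. The analysis would still not be intention-to-treat in either case.

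**The case against.** **One rule may have been meant for both arms.** The control sentence repeats the assurance of no penalty that the previous sentence has just explained in terms of data. A reader might infer that drop-outs are definitely removed from one arm only. The documents do not establish that. It is the literal reading, but the text never says that control leavers' data will be kept. This part of the objection stands: the asymmetry is possible, not proven. It does not touch the conflict with intention-to-treat.

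**The rule concerns leaving the study, not skipping sessions.** Students who stop modules but remain in follow-up are not covered by its words, and Section 6.2 plans to contact participants to complete follow-up. This is fair, but the rule stands under a heading about discontinuing the allocated intervention, and nothing separates stopping sessions, leaving follow-up and revoking consent to data use. Staff could apply it too widely.

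**The bias figures are soft.** A reader might take the 0.10 to 0.20 SD rows as the expected bias in favour of the intervention, on the plan's own 20% loss. The documents do not support that reading. Students who are merely unreachable have not elected to leave and would be imputed. No withdrawal rate, leaver–stayer gap or direction is given. For those who leave before three months, keeping earlier data recovers only the part of the gap that those data predict. The model also compares change from baseline, so a gap already present at baseline does not carry over one for one. All of this stands, and it makes the figures a ceiling.

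**Consent may require the exclusion.** The consent and assent forms are not shown and may promise it. A corrected rule can still honour explicit revocation.

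**Conclusion.** The contradiction holds and depends on no figure. Section 3.3 fixes an exclusion that is incompatible with the intention-to-treat analysis in Sections 7.1 and 7.4 and removes the material that the imputation in Section 7.4 needs. This is a stated rule, not a detail left for an analysis plan. It decides who enters the primary analysis, so it must be corrected.

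The size cannot be determined from the documents. The conditional ceiling is about 0.05 to 0.20 SD. It rests on three assumptions: 20% of one arm removed, leavers 0.25 to 1.0 SD worse than stayers, and controls fully retained. The bias favours the intervention if leavers do worse and disfavours it if they do better. Under a symmetric rule the one-arm figures do not apply.

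**What to change.** Replace the sentence in Section 3.3 with one rule for both arms:

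- Data collected up to withdrawal are kept and analysed in the allocated arm. Later missing scores are handled by the multiple imputation of Section 7.4.
- Students who only stop attending sessions remain in the study and are still offered the follow-up questionnaires.
- Data are removed only where the student or parent explicitly revokes consent to their use. Such removals are counted and reported by arm.

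The change is one paragraph and needs no additional students or procedures. The consent and assent wording must be aligned with it and the ethics committee notified. Section 8.5 foresees such notice, and additional consent if needed. It should be made before students begin to leave, because excluded data may not be recoverable later.

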### 3.4. Strategies to Improve Adherence to Interventions

Adherence to the intervention will be monitored by research assistants from the research team. School psychologists will fill out a small survey after each session informing the attendance of students and information about the quality of the delivery. Research assistants will be in close contact with school authorities and school psychologists, monitoring the progression of the program during study visits.

### 3.5. Provisions for Post-Trial Care

There is no potential harm or damage in this trial. The intervention group will receive an evidence-based intervention and the control group will receive the usual care in health centers.

### 3.6. Outcomes

Self-report questionnaires assessing primary and secondary outcomes will be administered at baseline (one week before the start of the intervention), at post-intervention, and follow-up (3, 6 and 12 months). Primary and secondary outcomes will be measured electronically using Qualtrics.

Participants will be asked sociodemographic information including, age, sex at birth, gender, race/ethnicity, education, family income, and psychological/psychiatric treatment.

#### 3.6.1. Primary Outcome

The primary outcome (suicide ideation) will be assessed by the Suicidal Ideation Questionnaire (SIQ) [63], a 15-item self-report measure designed to determine SI in adolescents. Scores are ranked 0–6, with higher scores indicating greater severity of suicidal ideation. The maximum score is 90 and a cut-off score of 31 indicates a clinically meaningful level of suicidal ideation. It has been validated with clinical and non-clinical populations and has shown high levels of internal consistency (α > 0.90) and test–retest reliability (α > 0.90) and high levels of construct and criterion validity [64].

#### 3.6.2. Secondary Outcomes and Questionnaires

Suicide attempt: two questions assessing whether participants had attempted suicide; if yes, how many attempts?

Anxiety as trait and as state: The State–Trait Anxiety Inventory (STAI-X) [65] is a self-report questionnaire with two scales of 20 items, each assessing state and trait levels of anxiety. Respondents indicate how they generally feel on a 4-point Likert scale from 0 (almost never) to 3 (almost always). The minimum score is 0 and the maximum score is 60 for both scales. Higher scores mean higher trait or state anxiety levels. It has been validated in the Chilean population aged 13–60 years old [66].

Hopelessness: The Beck Hopelessness Scale [67] is a self-report scale with 20 true or false items, nine of which are keyed ‘false’ and 11 are keyed ‘true’. For every statement, each response is assigned a score of 0 or 1 and the total hopelessness score is the sum of the scores on the individual items. The minimum score is 0 and the maximum score is 20. A higher score means higher hopelessness levels.

Social problem solving: The short form of the Social Problem-Solving Inventory Revised (SPSI-R Short Form) [68] is a 25-item self-report instrument measuring two adaptive problem-solving dimensions (positive problem orientation and rational problem solving) and three dysfunctional dimensions (negative problem orientation, impulsivity/carelessness style, and avoidance style). Each item is rated on a 5-point scale ranging from ‘not at all true of me’ (0) to ‘extremely true of me’ (4). The minimum score is 0 and the maximum score is 75. A higher score means a higher social problem-solving capability.

Cognitive-behavioral skills: The Cognitive-Behavioral Therapy Skills Questionnaire (CBTS) [69] is a 16-item scale with two scales measuring two skills: cognitive restructuring (CR) and behavioral activation (BA). Respondents rank each item on a 5-point Likert scale from 1 (I don’t do this) to 5 (I always do this). The minimum score is 15 and the maximum score is 80. A higher score means a higher presence of cognitive-behavioral skills. To assess general CBT skills, we have removed those items that refer exclusively to the practice of CBT sessions (e.g., keep track of the signs and symptoms of my condition); therefore, general CBT skills could be assessed before and after the intervention in both groups. 

Emotional regulation: The Emotion Regulation Questionnaire for Children and Adolescents (ERQ-CA) [70] is a 10-item self-report scale assessing two ER styles: Cognitive Reappraisal (CR, six items) Expressive Suppression (ES, four items). Items are rated on a 5-point Likert scale ranging from ‘strongly disagree’ (1) to ‘strongly agree’ (5). The minimum score is 10 and the maximum score is 50. A higher score means a higher presence of emotional regulation styles.

Adherence to TAU actions: A research assistant will register all the appointments and attendance of referred students to the primary care clinics. We will assess aspects related to the adherence to the actions included in the TAU.

### 3.7. Participant Timeline

Table 1 shows the participant timeline.

